**Methods:**

This study will have quantitative and qualitative components. The quantitative component will be a three-arm, observer-blind, placebo-controlled, interventional study of co-administration of SMC and anthelminthic drugs to pre-school and school-age children in Saraya district, southeast Senegal. Six hundred children aged 1–14 years will be randomly assigned to receive either SMC drugs only, SMC drugs and praziquantel or SMC drugs and albendazole and praziquantel at a ratio of 1:1:1. The primary outcome will be solicited and unsolicited adverse reactions to the study medications. The secondary outcomes will be the prevalence and intensity of *Plasmodium*-helminth co-infection and the prevalence of anaemia and mean haemoglobin concentration.

The qualitative component of the study will include the conduct of structured interviews to assess the acceptability, feasibility, enablers and barriers to the combined use of anthelminthic and SMC drugs among randomly selected parents/caregivers of children enrolled in the study and health care workers responsible for the delivery of the combined services.

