The geographical overlap in the co-endemicity of helminths and malaria parasites may result in synergistic or antagonistic interactions between helminths and malaria parasites [2, 9, 10]. There is some evidence that infections with *Schistosomes* and STH exert deleterious effects on the course and outcome of clinical malaria [3, 9]. Prominent among the clinical outcomes of malaria-helminth co-infections among children living in SSA is anaemia [11, 12] resulting from blood loss, haemolysis, inflammatory processes or splenic sequestration [13, 14]. The additive effects of malaria-helminth co-infection on haemoglobin concentration probably contribute significantly to mortality from malaria in children in SSA [11, 15]. Also, a substantial proportion of malaria mortality in children is linked to anaemia [16], while iron deficiency anaemia (IDA) induced by helminth infestations is associated with stunted growth, impaired cognitive development, poor school attendance and low academic performance [15, 16].

Given this context, it is important to develop a treatment approach that combines malaria and helminth control in an integrated framework that is safe, effective and easy to deliver. This study will investigate the feasibility and effectiveness of co-administration of anthelminthic and SMC drugs in a high-risk paediatric population living in a malaria-helminth co-endemic setting of Senegal, West Africa. This study is designed to test the hypothesis that co-administration of SMC and anthelminthic drugs will be safe and tolerated among children aged 1–14 years and that the incidence of side effects will not be significantly higher in children who receive the combined SMC and anthelminthic drugs than in those who receive SMC alone. The study will also seek to establish the extent to which combined administration of SMC and anthelminthic drugs will reduce the prevalence of anaemia, malaria and schistosomiasis compared to SMC administration alone.

Given that the feasibility of delivery and the effectiveness of an intervention may be influenced by its acceptability by end-users and other stakeholders, the perceptions of parents/caregivers of children enrolled in this study, SMC providers and programme managers will be explored to gain information on the acceptability, feasibility, barriers, enablers and practicalities of using the integrated SMC-anthelminthic approach.

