**Fig. 1 Fig1:**
[figure not shown]
Map of Senegal showing the study site. Source: https://www.cia.gov/resources/map/senegal/. Terms of use: https://www.cia.gov/site-policies

In June 2021, prior to the start of the malaria transmission season and before SMC administration commenced, we conducted a population-based survey to estimate the prevalence of malaria-helminth co-infections among children aged 1–14 years in 18 villages in Saraya district. Preliminary findings of this survey showed that the prevalence of malaria ranged between communities from 3.3 to 9.5% and of *Schistosome* infection from 12.2 to 64.8% (unpublished data). These findings will guide the selection of the villages for implementing the study described in this protocol. The schematic diagram of the study design is illustrated in Fig. 2.

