### Participant timeline {13}

#### Sample size {14}

Haemoglobin (Hb) concentration was used to calculate the sample size. Given that the mean Hb concentration in the SMC alone group in a previous study [18] in the same population was 10.5 g/dl, we assumed a mean Hb concentration of 11.0 g/dl in the SMC + anthelminth arm and a SD of the Hb concentration of 1.5 g/dl. To detect a mean difference between the treatment arms of 0.5 g/dl with 90% power at a 95% level of statistical significance, a minimum of 189 children per treatment arm will be needed. Allowing for 10% loss to follow-up, approximately 200 children will be enrolled into each treatment arm.

Based on a recent survey conducted in the study site (unpublished data), we assumed that the prevalence of any malaria or helminth infection in the SMC group will be 30%, the prevalence of any malaria or helminth infection in the SMC + anthelminth arms will be 16% and the relative risk will be 0.53 (that is, 47% reduction in the SMC + anthelminth arms compared to the SMC alone group). A minimum sample size of 188 children was considered sufficient to give 90% power at 95% confidence interval and 5% level of precision. Adding 10% loss to follow-up, approximately 200 children will be needed for each treatment arm. Therefore, a total of 600 children aged 1–14 years will be enrolled and randomly assigned at a ratio of 1:1:1 into the control and the two intervention arms.

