#### Plans for collection, laboratory evaluation and storage of biological specimens for genetic or molecular analysis in this trial/future use {33}

Prior to the administration of study drugs, finger-prick blood samples will be collected from the participants for preparation of thick and thin blood smears for malaria microscopy, and blood spots will be collected on Whatman filter papers for DNA isolation and PCR amplification for species determination. Freshly voided urine samples will also be collected from all study children. The urine filtration test will be used to quantify *S. haemotobium*, according to WHO guidelines. Parallel testing for circulating cathodic antigens (CCA) will be used to complement the filtration test [25]. The urine CCA dipstick test has been extensively used in SSA and has sensitivity and specificity values for *S. mansoni* ranging from 52.5 to 63.2% and 57.7 to 75.6%, respectively [26, 27].

Faecal samples will be collected to detect intestinal helminths. Duplicate Kato-Katz thick smears will be produced from the stool samples and examined by experienced technicians using light microscopy to determine the egg counts for *S. mansoni* and STH. The numbers of eggs per slide will be used to obtain a measure of the number of helminth eggs per gramme of faeces (EPG). The intensity of the helminth infection will be categorised according to WHO guidelines [28]. A multiplex PCR assay will also be used for simultaneous detection of mixed infections of helminths [29]. Quality control will be performed by re-examining at least 10% randomly selected blood slides, urine filters and Kato-Katz smears by an experienced independent lab scientist. Haemoglobin concentrations will be measured using the Haemocue® haemoglobin analyzer. Duplicate dried blood spots will be shipped to LSHTM for Luminex multiplex immunoassays [30].

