### Statistical methods

#### Statistical methods for primary and secondary outcomes {20a}

Infection intensities of positive samples will be calculated as the geometric mean of parasites per microlitre of blood for and geometric mean of eggs per gram of faeces for *S. mansoni*. For *S. haematobium*, infection intensity will be calculated as geometric mean of eggs per 10ml of urine. For pre- and post-intervention time points, the chi-square test will be used to compare proportions (prevalence) of malaria infection and prevalence of anaemia between the intervention and control groups. Similarly, for each time point, the Student *t*-test will be used to compare geometric mean parasite counts and mean haemoglobin concentrations between the intervention and control groups. The repeated measures analysis of variance will be used to compare geometric mean parasite counts and mean haemoglobin concentrations where repeated measurements for pre- and post-intervention time points are compared. All statistical tests will be two-sided at a significance of alpha < 0.05.

Qualitative data will be managed by NVivo software version 12.0 and analysis will be done by initially coding the main themes that emerge from the transcribed texts. The themes will subsequently be sorted and collated into categories and sub-categories. Hypotheses and concepts will be developed inductively from the themes. The findings of the qualitative and quantitative data addressing similar concepts will be triangulated in the final report.

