The global trend towards integrated, non-disease-specific approaches to controlling co-endemic diseases such as malaria and helminths has become an increasingly recognised strategy, but limited information exists on the safety, feasibility and effectiveness of combining SMC with helminth control at the community level [36, 37]. SMC involves administration of full treatment courses of antimalarial medications at monthly intervals during the malaria transmission to prevent malaria illness, with the objective of maintaining the therapeutic anti-malaria drug concentrations in the blood throughout the period of greatest malaria risk [31]. The approved preventive chemotherapy for mass drug administration (MDA) for STH and schistosomes (albendazole [ALB] and praziquantel [PZQ]) respectively, and the SMC drugs (AQ plus SP) work well with minimal side effects when used separately [35, 38]. Given that 4-aminoquinoline drugs are reported to have antagonistic pharmacokinetic interactions with praziquantel [39], the SMC partner drugs, AQ (a 4-aminoquinoline derivative) and SP will not be administered at the same time with anthelminthic drugs (albendazole and praziquantel) in this study. Because albendazole and praziquantel have a short half-life of 8.5 h and <2h respectively [22], anthelminthic drugs (praziquantel and albendazole) will be administered a day before the SMC drugs (AQ and SP) providing ample opportunity to objectively assess the tolerability of the different drug regimen.

The limitations of this study include the inability to mask the study drugs from parents and their children. Nevertheless, the use of control medications will ensure all study children receive equal number of medications and this could minimise bias due to unmasking. Also, the prevalence of malaria and STH is low in the study area and this may make it challenging to determine the effectiveness of the combined administration of SMC and anthelminthic drugs among the study participants but the study will provide important information on the safety and tolerability of administering SMC and antihelminthincs through a common delivery system. Measurement of efficacy is likely to require a larger study.

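### The 90% power for infection belongs to an either-infection composite that is neither a listed outcome nor in the planned tests; it does not carry over to the listed co-infection outcome

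*Protocol article*

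**What the plan says.** The Protocol article describes the infection endpoint differently in different places.

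- **Sample size {14}.** The second calculation concerns infection with either organism: "we assumed that the prevalence of any malaria or helminth infection in the SMC group will be 30" per cent, and "the prevalence of any malaria or helminth infection in the SMC + anthelminth arms will be 16" per cent. It gives a relative risk of 0.53, 188 per arm and 90% power.
- **Abstract (Methods) and Secondary outcomes {12}.** The infection outcome is the prevalence and intensity of Plasmodium-helminth co-infection; the Abstract's list ends "helminth co-infection and the prevalence of anaemia and mean haemoglobin concentration". The text under the same item in {12} adds egg counts for each helminth, and Plasmodium prevalence and intensity.
- **Background and rationale {6a} and Objectives {7}.** The aim is to learn how far combined treatment "will reduce the prevalence of anaemia, malaria and schistosomiasis compared to SMC administration alone". The secondary objective likewise names malaria, anaemia and helminth infections as separate items.
- **Statistical methods {20a}.** For prevalence, "the chi-square test will be used to compare proportions (prevalence) of malaria infection and prevalence of anaemia between the intervention and control groups". Student t-tests and repeated-measures analysis of variance cover geometric mean parasite counts and haemoglobin.

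The composite appears only in the sample-size paragraph.

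**The concern.** Power is a property of one endpoint and one test. Here the 90% is attached to an OR endpoint (either infection), while the headline infection outcome is an AND endpoint (both infections), which is necessarily rarer. A reader who takes the 90% as covering the infection outcome would read a null co-infection result as adequately powered evidence of no effect.

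The second consequence concerns the tests. Helminth prevalence, and schistosome prevalence in particular, is what the anthelminthics should change most directly, and it is a stated aim. Section {20a} specifies prevalence tests for two other conditions and none for this one. With the powered endpoint, the listed endpoint and the tested endpoints all different, it stays open until the data are in which infection result will be presented as the trial's answer.

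**Working it through.** **1. Reproduce the plan's figure.** Inputs from {14} and {20a}: p1 = 0.30, p2 = 0.16, two-sided alpha 0.05 (z = 1.960), power 90% (z = 1.2816). The mean proportion is 0.23 and the difference 0.14.

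n = [1.960 × √(2 × 0.23 × 0.77) + 1.2816 × √(0.30 × 0.70 + 0.16 × 0.84)]² / 0.14²
= (1.1665 + 0.7521)² / 0.0196 = 187.8, so 188 per arm.

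Power at 188 per arm is 90.0%. The calculation is correct for the composite. With 200 enrolled less 10% (180 per arm) it is 88.7%.

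**2. Inputs for co-infection.** The documents give no co-infection rate, so the following are assumptions.

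- Malaria: in the June 2021 survey described under Trial design {8}, "the prevalence of malaria ranged between communities from 3.3 to 9.5" per cent.
- Schistosome infection in the same survey: 12.2% to 64.8%.
- If the two infections are independent, co-infection lies between 0.033 × 0.122 = 0.0040 and 0.095 × 0.648 = 0.0616.
- If every malaria-positive child in the highest-prevalence community also carried helminths, it would be 0.095.
- Relative risk: the plan's 0.16 / 0.30 = 0.533, borrowed from the composite. As a sensitivity value, 0.25.
- 180 evaluable per arm.

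**3. Power.** Power = Φ{[|p1 − p2| − 1.960 × √(2p̄(1 − p̄)/n)] / √[(p1(1 − p1) + p2(1 − p2))/n]}, where p̄ is the mean of p1 and p2.

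| Control rate | Rate at RR 0.533 | Expected events per arm | Power, RR 0.533 | Power, RR 0.25 |
|---|---|---|---|---|
| 0.40% | 0.21% | 0.7 vs 0.4 | about 5% | about 8% |
| 6.16% | 3.28% | 11.1 vs 5.9 | about 25% | about 63% |
| 9.5% | 5.07% | 17.1 vs 9.1 | about 37% | about 82% |

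Exact enumeration at relative risk 0.533 agrees in the second and third rows (24.6% and 36.8%). In the first row, with less than one expected event per arm, the normal formula is unreliable and the exact power is about 0.5%. Comparing both anthelminthic arms together with control, at relative risk 0.533 and 9.5%, gives about 50%.

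**4. Match endpoints to tests.**

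| Endpoint | Listed outcome {12} | Between-arm test in {20a} | Power stated in {14} |
|---|---|---|---|
| Either infection | no | no | 90% |
| Co-infection prevalence | yes | no | no |
| Helminth or schistosome prevalence | egg counts recorded; prevalence is an aim in {6a} and {7} | prevalence no; counts yes | no |
| Malaria prevalence | yes, in the item's text | yes | no |
| Haemoglobin | yes | yes | 90% |

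The row with the infection power has neither a listing nor a test.

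**The case against.** The strongest reply is that co-infection is not the trial's only infection result. Section {12} records egg counts for each helminth and Plasmodium prevalence, and {20a} compares geometric mean parasite counts after defining intensity for both schistosome species. At the plan's relative risk and 180 per arm, schistosome prevalence alone would have about 46% power at 12.2%, 89% at an illustrative 30%, and over 99% at 64.8%. This stands: it would be wrong to say that the infection question rests on a handful of events, or that helminths are not compared at all. What is missing is a comparison of helminth prevalence and of the composite.

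It may also be said that an unseen analysis plan could supply those tests. It could, but it would not remove the mismatch between the powered and the listed endpoint, both of which the article states. Section {20a} also specifies tests for the other prevalences, and {20b} expects no further analyses.

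The trial's size is not in question. Haemoglobin has its own calculation (189 per arm), outcome and test, and the primary outcome is safety.

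Three stronger readings are tempting, and the documents do not support them.

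- **That 37% is the most power co-infection could have.** The survey figures are community extremes from before the season and before SMC, while the outcome is measured at the end of the season. The relative risk belongs to a different endpoint.
- **That false positives on the urine CCA test dilute the contrast.** Section {33} quotes sensitivity and specificity for S. mansoni "ranging from 52.5 to 63.2% and 57.7 to 75.6%, respectively", but says that CCA complements filtration and nowhere counts CCA-only positives as infection.
- **That the Discussion contradicts the 90%.** Its remark, "Measurement of efficacy is likely to require a larger study", follows a statement about low malaria and STH prevalence. It does not mention schistosomes, which could drive the composite.

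**Conclusion.** The point holds as a mismatch of endpoints, not as an arithmetical error. The 90% is right for the either-infection composite and belongs to no outcome that the article lists or tests. It cannot be read as the power for co-infection, which is about 5% to 25% under independence and about 37% at 9.5%, and reaches 63% to 82% (at 6.2% and 9.5%) only if the relative risk is as low as 0.25. These figures rest on pre-season survey ranges, 180 evaluable per arm and an assumed relative risk; they show scale and are not bounds. Infection is a secondary outcome, so the point should be corrected before analysis but does not touch the primary safety question or the haemoglobin comparison.

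**What to change.** Before analysis:

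1. Add the either-infection composite, measured at the end-of-season survey, as a secondary outcome in {12}, with malaria prevalence and Schistosoma prevalence also reported separately.
2. Add between-arm comparisons of the composite and of helminth prevalence to {20a}.
3. Keep co-infection as listed, and state that it is expected to be imprecisely estimated.
4. State in {14} that the 90% refers to the composite only.

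The cost is wording in the protocol and analysis plan, with no new samples, visits or participants. Trial status reports recruitment complete on 21 June 2022, so the added outcome should be dated and identified as an amendment made before the outcome data were analysed.

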### Recruitment {15}

#### Stakeholder engagement and community sensitisation

The PI and co-investigators in Senegal have held several meetings with the programme managers and national coordinators of the SMC and NTD programmes of the Senegal Ministry of Health about this study, and these officers have provided their support during the implementation of the first stage of this project involving two population-based surveys in 2021. The study team will meet again with the community leaders and other stakeholders in the host community. Community sensitisation and engagement meetings will be organised prior to the commencement of the study to explain the nature of the study to the parents/caregivers of potentially eligible children*.*

During these meetings, the study team will explain the need for this study, using a simple picture to illustrate the concurrent administration of SMC and anthelminthic drugs; the study rationale and informed consent procedure; and the risks and benefits of allowing their children to participate in the study. After these meetings, trained research staff will identify parents/caregivers of potential study participants to explain the study further to them on an individual basis. Parents/caregivers who feel that the study is appropriate for their child will be visited at home at a mutually agreed time. For logistical purpose, consent will be obtained from a parent/caregiver one day before the planned start date of the study. A research staff member will provide a pre-labelled stool collection cup to the parent/caregiver at this visit and encourage them to collect stool from their child and keep same safely for the research team who will visit them, the following day.

### Assignment of interventions: allocation

#### Sequence generation {16a}

Randomisation will be used to minimise bias in the assignment of eligible children to the study arms to increase the likelihood that known and unknown attributes (e.g. demographic and baseline characteristics) are evenly balanced across arms and to enhance the validity of possible statistical comparisons across arms. Randomisation will be performed by a study pharmacist in blocks of 3 using a table of random numbers and will be stratified by age groups.

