### Data collection and management

#### Plans for assessment and collection of outcomes {18a}

On the start day of the study, the research staff will confirm the parent/caregiver’s willingness to allow their child’s continued participation in the study and administer a purpose-designed electronic questionnaire to the parents/caregivers. The questionnaire will cover information such as socio-demographic, health and residence characteristics, history of de-worming and prior malaria treatment. Height/length (cm) and weight (kg) of each child will be measured and anthropometric indices, height-for-age, weight-for-age, weight-for-height and body mass index, will be calculated using the WHO AnthroPlus software (www.who.int/growthref/tools/en/). The study villages will be mapped by recording each study participant’s household global positioning system (GPS) coordinates with a hand-held GPS device.

The quantitative study will be implemented in collaboration with the SMC and NTD providers during the SMC campaign which will start in Saraya district by the middle of June 2022. Two hundred children pre-school and school-age children will be enrolled into each arm of the study as described above. The study procedures are illustrated in Fig. 2 and Table 2. The children will be evaluated one  month after the last course of SMC cycles at the end of malaria transmission season to measure haemoglobin concentration and to obtain a further blood film, dried blood spot, stool and urine samples.

**Table 2 Tab2:** Schematic diagram of the study procedures

SMC cycle	1					2, 3 and 4	End of malaria season
Timelines (days)	Day 0–1	Day 0	Day 1	Days 2 and 3	Days 4–6		
**Study procedures**						**Passive surveillance**	
Informed consent ± assent	X						
Enrolment and questionnaire administration to parent/caregivers		X					
Distribution of collecting bottles for stool sample	X						
Sample collection (finger-prick blood, urine, stool)		X					
**Randomisation**		X					
Group 1: vitamin A + zinc		X	AQ + SP	AQ			
Group 2: PZQ + vitamin A		X	AQ + SP	AQ			
Group 3: ALB + PZQ		X	AQ + SP	AQ			
Safety assessments		X	X	X	X		
**Post-intervention survey**							X
Sample collection: finger-prick							X
Sample collection: stool							X
Sample collection: urine							X

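### The named tests have no village or age-group term although surveyed communities ranged from 12.2% to 64.8% in schistosome prevalence: a modest, avoidable loss of precision in the secondary outcomes

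*Protocol article*

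**What the plan says.** Under Sequence generation {16a}, randomisation "will be performed by a study pharmacist in blocks of 3 using a table of random numbers and will be stratified by age groups". Age group is the only stratification factor named.

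Under Trial design {8}, the 2021 survey was done "among children aged 1–14 years in 18 villages in Saraya district". It found schistosome "infection from 12.2 to 64.8% (unpublished data"), and malaria prevalence from 3.3% to 9.5%, between communities. The text adds: "These findings will guide the selection of the villages for implementing the study described in this protocol". It does not give the number of villages selected or their prevalences.

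Under Statistical methods {20a}, "the chi-square test will be used to compare proportions (prevalence) of malaria infection and prevalence of anaemia between the intervention and control groups". For continuous outcomes, the Student t-test "will be used to compare geometric mean parasite counts and mean haemoglobin concentrations between the intervention and control groups" at each time point, with repeated-measures analysis of variance where pre- and post-intervention values are compared. None of these has a village or age-group term. No test is named for helminth prevalence.

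Plans for assessment {18a} has the coordinates of each participant's household recorded, so village is known for every child.

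**The concern.** Between communities, the protocol's own survey shows a five-fold range in schistosome prevalence (64.8/12.2 = 5.3). Where a child lives is therefore a known predictor of helminth infection. It also bears on re-exposure between the single anthelminthic treatment and the end-of-season survey.

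A test that ignores such a factor leaves its variance in the arm comparison. If the arms differ by chance in village mix, that difference enters the estimate. If the arms happen to be balanced by village, the test still counts village variance as noise and is conservative. The same holds in principle for age group, which is used to balance the arms and then left out of the tests.

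The matter has some weight because the secondary outcomes have no reserve: 200 per arm less 10% leaves 180, below the stated minimums of 188 and 189.

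**Working it through.** **1. The plan's own figures (Sample size {14}).**
- Infection, 30% v 16%, two-sided 5%, 90% power, pooled variance: n = [1.96·√(2·0.23·0.77) + 1.2816·√(0.30·0.70 + 0.16·0.84)]² / 0.14² = (1.166 + 0.752)² / 0.0196 ≈ 188 per arm. This matches the stated 188.
- Haemoglobin, difference 0.5, SD 1.5: n = 2·(1.96 + 1.2816)²·1.5²/0.5² = 189.1, against the stated 189.
- With 180 per arm, power is 88.7% (infection) and 88.5% (haemoglobin) before village is considered.

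**2. Share of the variance that village explains.** Share = variance of village prevalences / [p̄(1 − p̄)]. The number and spread of trial villages are assumptions: equal-sized villages, evenly spaced.
- Survey range 12.2-64.8%, mean 38.5%: 29% with two villages at the extremes, 16% with 4, 14% with 6, 12% with 10.
- Narrower selections (20-50% or 40-65%, 4 to 18 villages): about 2-6%.
- Survey range scaled to the planned 30% control mean (factor 30/38.5, giving 9.5-50.5%): 0.0420/0.21 = 20% with 2 villages, 0.0196/0.21 = 9% with 6, 0.0171/0.21 = 8% with 10.

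**3. Power at 180 per arm.** Simulated individual randomisation without village stratification, 6,000 trials per scenario (Monte Carlo standard error about √(0.9·0.1/6000) = 0.4 points).

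| Scenario | Chi-square | Mantel-Haenszel by village |
|---|---|---|
| 30% v 16%, scaled range, 6 or 10 villages | about 89-90% | about 90-91% |
| 30% v 16%, scaled range, 2 villages | about 89% | about 93% |
| Relative risk 0.65, full range, 4 to 10 villages | about 79% | 82-84% |
| Relative risk 0.65, full range, 2 villages | 77% | 87% |

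The two-village rows are an extreme that nothing in the document supports. They mark the upper limit.

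**4. Validity.** With no treatment effect and no village stratification, the unadjusted test rejected in about 5% of trials (4.5-5.5%) in every scenario.

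**5. Chance imbalance depends on enrolment order, which is not stated.**
- If the blocks do not follow villages, the SD of the arm difference in expected prevalence is village SD·√(2/200). That is 0.152·0.1 = 1.5 points for an even spread and 0.263·0.1 = 2.6 points for two extremes.
- If blocks of 3 are filled village by village (600 children, three age strata assumed), simulation gives an SD of 0.33, 0.20 and 0.18 points for 2, 6 and 10 villages.

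**6. The balanced case.** If the arms are balanced by village, the true variance of the difference is (1 − share) times what the chi-square test assumes. The actual level is then 2·[1 − Φ(1.96/√(1 − share))]. With the scaled shares of 20%, 9% and 8% this gives 2.8%, 4.0% and 4.1%, so about 3-4% in place of 5%.

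**The case against.** The strongest reply is that nothing here is wrong. Children are randomised individually, the tests hold their level, and covariate adjustment is often settled in a statistical analysis plan, which is not shown. The article also condenses a longer protocol. Part of this stands: the missing village term does not prove that none is planned. But {20a} does not leave the method open. It names specific unadjusted tests, and those can be judged as stated.

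Several further replies limit the size, and they stand:
- The 12.2-64.8% range is from the survey before villages were selected; the trial villages may differ less.
- The wide range is for schistosomes. The chi-square test is named for malaria and anaemia, malaria ranged only from 3.3% to 9.5%, and no village variation is given for anaemia or haemoglobin. No gain can be quantified for those outcomes.
- These are secondary outcomes. The primary outcome is adverse events, and the Discussion already says that efficacy probably needs a larger study.
- Recruitment closed on 21 June 2022 (Trial status), so the allocation cannot be changed.

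A reader might infer that village clustering makes the tests invalid, or that the sample size needs a design effect. The document does not support this: allocation is by child, and the simulated type I error stays at about 5%. A reader might also infer that an arm imbalance of 1.5-2.6 points (SD) is to be expected. That holds only if the blocks of 3 cut across villages. Home visits and a recruitment window of a few days make village-by-village enrolment possible, and imbalance would then be small.

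**Conclusion.** The point holds as a modest and avoidable loss of precision in the secondary outcomes, chiefly helminth infection. It is neither bias nor an invalid test. At the planned effect the village term is worth about 1 to 2 points of power with 6 to 10 villages and about 4 in the two-village extreme. It is worth less if village selection narrowed the range. That is enough to bring power at 180 per arm back to about 90% in most of the scenarios examined.

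The term helps or is neutral under either enrolment order. It recovers precision if the arms are unbalanced by village, and restores the nominal level if they are balanced. These sizes rest on assumed numbers, sizes and prevalences of villages. For age group the argument is the same in kind, but the document gives no figures from which to size it.

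**What to change.** In Statistical methods {20a}, compare infection prevalence (helminth as well as malaria) between arms with a Mantel-Haenszel test stratified by village and age group, or a binary regression adjusted for both. Treat anaemia in the same way. Include village and age group in the haemoglobin model. Fix this, with a rule for pooling very small villages, before the end-of-season data are analysed.

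The cost is one or two sentences and slightly more analysis work; household location is already recorded. Stratifying the allocation list by village as well as age group is advice for a future trial only.
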